### Statistical analysis

The study will be carried out in accordance with the CONSORT guidelines. All analyses will be based on the intention-to-treat sample and missing values will be imputed by means of regression analyses. A t-test will be used to compare the post-test mean scores (at T_1 _and T_0_) for the intervention group with the post-test mean scores for the control group. For comparison of the two means Cohen's *d *will be used as the between effect size. Cohen's *d *will be calculated as the difference between the post-test mean scores of the intervention and the control group divided by the pooled standard deviation. Effect sizes of 0.8 are assumed to be large; effect sizes of 0.5 are moderate; and effect sizes of 0.2 are assumed to be small [51].

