### Sample size

The sample size will be based on the expected difference of d = 0.45 on the primary outcome between the experimental and control groups. This expected difference is based on previous studies [10,11]. Based on a power (1-beta) of 0.80 in a two-tailed test, an alpha of 0.05, we need to start with 100 participants at baseline in each condition to show an effect-size of 0.45. The total sample size at baseline therefore, is determined as being 200 participants with depressive complaints.

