### Assessments

All assessments will take place in the preferred language, either Dutch or Turkish. The primary outcome measure is the reduction of depression symptoms as measured by the CES-D, the secondary outcome measures are symptoms of anxiety, somatic symptoms, acculturation, quality of life and satisfaction.

The CES-D, one item on the Beck Depression Inventory-II (BDI-II) and Section C of the Mini-International Neuropsychiatric Interview (M.I.N.I) will be administered as screening measures. Suicide ideations and risk will be measured in two steps. Suicide ideations and risk will be measured in two steps. First, the suicide item on the BDI-II will be presented [23,24]. This instrument is validated among Dutch (e.g. [25,26]] and Turkish populations [27,28]. If the response is confirming, then the suicide risk will be measured with the suicidality section of the MINI [29,30]. The suicide section of the MINI consists of six items and quantifies respondents in four groups: no suicide risk, low suicide risk, moderate suicide risk and high suicide risk. Dutch [31] and Turkish [32] translations of the MINI will be used.

Assessments will take place before randomization (T_0_), after completing the treatment (6-8 weeks, T_1_), and four months after baseline (T_2_). An overview of the procedures the participants will undergo in this study is given in Figure 1. See table 1 for an overview of all assessments at each point in time.

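### Regression imputation followed by an ordinary t-test carries no imputation uncertainty: depending on the imputation model, it inflates type I error or dilutes the treatment effect

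*Protocol article*

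**What the plan says.** The Statistical analysis section of the protocol article lays out a chain of four steps:

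- Analysis set: "All analyses will be based on the intention-to-treat sample".
- Missing data: "missing values will be imputed by means of regression analyses".
- Test: "A t-test will be used to compare the post-test mean scores" between the two arms.
- Effect size: Cohen's d is the difference in post-test means "divided by the pooled standard deviation".

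The section does not say whether imputation is single or multiple, whether random residuals are added, which predictors are used, or whether arm is one of them. It mentions no pooling over imputed data sets and no variance correction.

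The Sample size section bears on how much data might be imputed. It powers the trial on d = 0.45 and says "we need to start with 100 participants at baseline in each condition", but gives no dropout rate.

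**The concern.** Under intention to treat, every randomised participant without a post-test score enters the primary test with a value predicted by a regression. A t-test on the completed data counts that prediction as one more independent observation. Two things then go wrong when arm is a predictor. The imputed values add no information, yet they count in the sample size behind the standard error. If they are pure predictions, they also vary less than real scores, so the pooled SD shrinks. When arm is not a predictor, both arms are filled in from the same line, and the imputed participants contribute no treatment difference at all.

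At stake are the primary p-value, the confidence interval and the headline d, which is also the quantity on which the trial was sized.

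**Working it through.** **Sample size, as background.** Inputs from the Sample size section: d = 0.45, power 0.80, two-sided alpha 0.05. The normal approximation gives n = 2(1.960 + 0.842)²/0.45² = 77.5, so 78 per arm. The exact t-test gives 78.5, so 79. The stated 100 is not reproduced without an allowance for loss; 1 − 79/100 = 21% would account for it. The article does not state that rate, so it serves here only as a plausible value within a range.

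**Assumptions.** 100 per arm (document). Outcome SD 1 within arm. Fraction missing m = 10–40% in both arms, completely at random. Baseline-outcome CES-D correlation r = 0.3–0.7. Baseline is available as a predictor because the first assessment precedes randomisation (Assessments section).

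**Closed-form check, pure predictions with arm in the model.**

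- Variance of the completed scores within arm: (1 − m) + m·r².
- Standard error the t-test reports: √(2 × that variance/100).
- Actual SD of the estimated difference: √(2[r²/100 + (1 − r²)/(100(1 − m))]).
- True type I error: about 2 × [1 − Φ(1.972 × reported SE/actual SD)], where 1.972 is the t critical value on 198 df.
- Expected d: 0.45/√(variance of completed scores).

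For m = 0.21, r = 0.5: variance = 0.79 + 0.0525 = 0.8425, SD 0.918. Reported SE = √(0.01685) = 0.130. Actual SD = √(2[0.0025 + 0.75/79]) = 0.155. The ratio is 0.838, so the effective critical value is 1.653 and type I error is about 9.8%. Expected d = 0.45/0.918 = 0.49.

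**Arm omitted.** Imputed participants contribute no difference, so the expected mean difference is 0.45(1 − m): 0.45 × 0.79 = 0.36 at 21% missing and 0.45 × 0.60 = 0.27 at 40%.

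**Simulation over the range.** 5,000 null trials per cell for type I error and 1,500 trials at d = 0.45 for mean d; ranges run over r = 0.3, 0.5 and 0.7.

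| Missing | Arm in model, no residuals: type I error | d for true 0.45 | Arm in model, one draw with residuals: type I error | Arm omitted, no residuals: type I error | d for true 0.45 |
|---|---|---|---|---|---|
| 10% | 7.0–7.7% | 0.47–0.48 | 6.5–7.6% | 4.7–5.2% | 0.42–0.43 |
| 20% | 7.3–11.6% | 0.48–0.50 | 8.3–10.0% | 4.9–5.4% | 0.38–0.39 |
| 30% | 10.3–15.7% | 0.50–0.53 | 10.1–12.2% | 4.9–5.2% | 0.34–0.37 |
| 40% | 13.8–23.1% | 0.51–0.57 | 12.1–16.5% | 4.6–5.3% | 0.30–0.33 |

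With residuals added and arm in the model, d stays close to 0.45 (0.445–0.458); only the test is wrong. The closed form agrees with the simulation: at m = 0.20, r = 0.5 it gives a reported SE of 0.130, an actual SD of 0.154 and 9.5% type I error, against simulated values of 0.130, 0.152 and 9.2%.

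**Comparator.** Multiple imputation with arm in the model, 20 imputations and Rubin's rules, r = 0.5 (2,500 null trials and 1,000 at d = 0.45):

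| Missing | Type I error | Mean SE | Actual SD | Mean d |
|---|---|---|---|---|
| 20% | 5.2% | 0.155 | 0.158 | 0.454 |
| 40% | 4.6% | 0.176 | 0.174 | 0.442 |

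**The case against.** The strongest reply is that the article never says single imputation. Regression-based multiple imputation fits the wording too, and an article may leave the number of imputations, the predictors and the pooling to the full protocol or analysis plan. The first part stands: single imputation is a face-value reading, not a quotation. The second part does not dispose of the point. The article does state a sequence, from imputation to t-test to pooled SD, and nothing in that sequence suggests several data sets or pooled variances.

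A reader might infer that type I error necessarily exceeds 5% and that d is necessarily overstated. The article does not support that. Whether arm is a predictor is not stated; without it, type I error stays near 5% and the harm is attenuation. With arm and added residuals, d is about unbiased. The harms are alternatives, and the text does not show which applies.

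A reader might also take 21% loss as the plan's own figure. It is only back-calculated from 100 and 79; the 30% and 40% rows likewise have no basis in the article and only show the range.

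Finally, a mixed model would change the planned test rather than clarify it. That is fair, which is why it is offered only as an alternative.

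**Conclusion.** The concern holds in conditional form. As written, the primary analysis treats regression-filled scores as observed data. None of the three single-imputation variants checked gives both a valid test and an unbiased effect:

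- Arm included: type I error is about 7% with 10% missing, 7–12% with about 20%, and 12–23% with 40%. Without residuals, d is also overstated.
- Arm omitted: the test keeps its level, but the effect is diluted in proportion to the fraction missing.

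The sizes rest on assumed missing rates, data missing completely at random and correlations of 0.3–0.7. The mechanism assumed is a benign one, and the method already fails under it. If multiple imputation was intended, one sentence saying so, with arm in the model and the pooling rule, would settle the matter.

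**What to change.** In the Statistical analysis section, replace the imputation step with multiple imputation: arm, baseline CES-D and the CES-D at the other follow-up time in the model, and at least 20 imputations. Run the planned between-arm comparison in each data set and pool by Rubin's rules. A likelihood-based mixed model using all observed T1 and T2 scores is an acceptable alternative.

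Compute d from the pooled difference and an SD that is not shrunk by deterministic predictions: either the SD of observed scores or the within-imputation SD under multiple imputation, which gave nearly unbiased d in the check above.

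No new data are needed, since CES-D is scheduled at T0, T1 and T2 (Table 1). The cost is a little programming and somewhat wider confidence intervals; at r = 0.5 and 20% missing, the mean standard error goes from 0.130 (pure predictions, arm in the model) to 0.155, close to the true spread of the estimate.

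### The only stated between-arm test ignores baseline CES-D, which every randomised participant has; adjusting for it would add precision at no cost

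*Protocol article*

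**What the plan says.** All places are in the Methods of the protocol article.

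- **Statistical analysis, test.** "A t-test will be used to compare the post-test mean scores", set out as scores "for the intervention group with the post-test mean scores for the control group". The time points given in brackets are T1 and T0. No covariate, change score, ANCOVA or mixed model is named.
- **Statistical analysis, effect size.** "Cohen's *d *will be calculated as the difference between the post-test mean scores of the intervention and the control group". The denominator is the pooled SD.
- **Assessments.** "The primary outcome measure is the reduction of depression symptoms as measured by the CES-D". T0 is placed before randomisation, T1 at 6-8 weeks and T2 at four months.
- **Inclusion and exclusion criteria.** A CES-D score of at least 16 is required for entry.
- **Table 1.** CES-D, HADS anxiety, SCL-90 somatic symptoms, LAS and EQ-5D are all scheduled at T0, T1 and T2.
- **Randomization.** No stratification on baseline severity is mentioned.
- **Sample size.** The basis is an "expected difference of d = 0.45 on the primary outcome" with 80% power and two-sided alpha 0.05, giving 100 per arm at baseline.

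**The concern.** The baseline value of the same scale is usually among the best predictors of the follow-up score. Here it is collected before allocation, and eligibility guarantees that it is complete. A comparison of raw post-test means makes no use of it. Two things are lost:

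- **Precision.** The part of the outcome variance that baseline could explain stays in the standard error.
- **Protection against chance imbalance.** If one arm happens to start with higher CES-D scores, part of that gap passes into the estimated effect. The article describes nothing in the design or the analysis that would counter this.

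The precision matters most if follow-up losses are heavy, because the observed sample could then fall below what the unadjusted test needs.

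The bracketed time points add a separate difficulty. T0 cannot be a post-test, so a reader cannot tell whether T2 was meant, whether a baseline comparison was meant, or whether some form of change was intended.

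**Working it through.** **Inputs from the document.** d = 0.45 (so SD = 1 on the standardised scale), power 0.80, two-sided alpha 0.05, 100 per arm (all from Sample size).

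**Assumed inputs.** The correlation r between baseline and post-test CES-D is not given; 0.3 to 0.6 is used. Entry at CES-D 16 or above restricts the baseline range, which may put r towards the low end. Attrition is not given either; 60 analysed per arm stands for an assumed 40% loss, 100 × (1 − 0.40) = 60.

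**Step 1: the plan's own figure.** The number per arm is 2(1.960 + 0.842)² / 0.45² = 77.5, so 78 by the normal approximation and 79 by the exact t calculation. The stated 100 is larger. It matches an unstated loss of about 21% (79 / 0.79 = 100). With all 100 per arm analysed, the unadjusted t-test has power 0.89. The missing attrition allowance is a separate matter and does not affect this point.

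**Step 2: effect of adjustment.** ANCOVA multiplies the residual variance by 1 − r².

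- r = 0.3: 1 − 0.09 = 0.91, variance down 9%, standard error down 4.6%.
- r = 0.6: 1 − 0.36 = 0.64, variance down 36%, standard error down 20%.

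Power is the two-sample t power at d / √(1 − r²), with one degree of freedom spent on the covariate. The standardised effect becomes 0.45 / √0.91 = 0.472 at r = 0.3 and 0.45 / √0.64 = 0.5625 at r = 0.6.

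| Analysed per arm | Unadjusted | r = 0.3 | r = 0.4 | r = 0.5 | r = 0.6 |
|---|---|---|---|---|---|
| 100 (planned) | 0.89 | 0.91 | 0.93 | 0.96 | 0.98 |
| 79 (needed by the stated inputs) | 0.80 | 0.84 | 0.87 | 0.90 | 0.94 |
| 60 (assumed 40% loss) | 0.69 | 0.73 | 0.76 | 0.81 | 0.86 |

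**Step 3: chance imbalance.** With 100 per arm, the difference in baseline means has standard error √(2/100) = 0.141 SD. An imbalance of 1.96 standard errors is 0.277 SD. The unadjusted estimate moves by r times this: 0.083 SD at r = 0.3, 0.139 SD at r = 0.5 and 0.166 SD at r = 0.6. At r = 0.5 that is 0.139 / 0.45 = 31% of the target effect. An imbalance this large is uncommon; one of a single standard error moves the estimate by 0.071 SD at r = 0.5.

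**Step 4: why not simply test change scores.** A change score has variance 2(1 − r) relative to the post-test score. At r = 0.3 this is 1.4, and power with 79 per arm falls to 0.66. At r = 0.5 it equals the post-test comparison, and only above that does it do better. ANCOVA is at least as precise as either, apart from the one degree of freedom.

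**The case against.** The strongest reply is that nothing here is invalid. Under randomisation the t-test is unbiased on average and holds its type I error, and its standard error already allows for chance imbalance. That stands.

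A reader might also infer that, because the outcome is worded as a reduction, a comparison of post-test means fails to estimate it. The document does not support that reading. Expected baseline means are equal in randomised arms, so the between-arm difference in mean reduction equals the between-arm difference in mean post-test score. The two approaches differ in precision, not in target.

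A further reply is that the trial is adequately powered as planned. This also stands: with 100 analysed per arm, power is 0.89 without adjustment, and it stays at about 0.80 until fewer than 79 per arm contribute. The size of the gain depends on a correlation that the document does not give, and at r = 0.3 the gain is small. Imputation keeps everyone in the intention-to-treat set, but it adds no observed outcomes and does not adjust the comparison.

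Finally, a condensed article may leave covariates to an analysis plan. That carries limited weight, because this article does name its test and its effect size, and both are unadjusted. It does not call the t-test primary, but it states no other between-arm test.

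**Conclusion.** The point holds as a free improvement. The stated analysis is valid and aims at the right difference, but it discards a complete, pre-randomisation covariate.

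For an assumed r of 0.3 to 0.6, the gain in power is about 3 to 9 percentage points at the planned 100 per arm, about 4 to 14 at 79, and about 4 to 18 at 60. The low end is quite possible because entry is restricted to CES-D 16 or above. Adjustment is not needed to reach 80% power unless losses take the analysed number below about 79 per arm. Where they do, it recovers power to an extent that depends on r: at 60 per arm, r of about 0.5 is needed to get back to 0.81.

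The bracketed T1 and T0 label is an error or ambiguity in its own right. Read literally, it adds a baseline comparison; it does not turn the test into a change-score or baseline-adjusted analysis.

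**What to change.** - Analyse CES-D at each post-baseline time point (T1 and T2) by ANCOVA on arm with baseline CES-D as covariate, or by an equivalent mixed model.
- Report the adjusted mean difference with its 95% CI, and derive the standardised effect size from that difference, stating which SD is used.
- Treat HADS anxiety, SCL-90 somatic symptoms, LAS and EQ-5D in the same way, each with its own T0 value. These are scheduled at T0 but are not entry criteria, so say how a missing baseline value would be handled.
- Correct the time points in the t-test sentence, since T0 is baseline.

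The cost is wording only. No further participants, visits or instruments are needed, because Table 1 already schedules every covariate. The change should be fixed before outcome data are seen, so that the choice between adjusted and unadjusted results cannot depend on them.

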## Discussion

A substantial part of the Dutch population has a Turkish background. They have a high prevalence of mental health disorders and have a high threshold for seeking professional help for these problems, but providing psychological help through the Internet may lower this threshold. This study evaluates the effectiveness of a guided self-help problem-solving intervention for depressed Turkish migrants that is culturally adapted and web-based. The strengths and limitations of the study can be summarized as follows:

Much is still not known about the effectiveness of internet interventions for depression in ethnic groups. By examining the effectiveness of a problem-solving treatment on the Internet for Turkish adults in the Netherlands, important information about psychological treatments in an ethnic minority group will be gathered. This will be highly relevant for clinicians and mental health services in improving the quality and the effectiveness of offering professional help.

A second strength of this study is that the intervention is available in two languages, which provides the flexibility of choosing the language of preference for receiving professional help. Turkish migrants who were previously unable to seek help because of the language barrier can now be treated. Moreover, by using the Internet to offer help, those who have a high threshold for seeking help can be reached and benefit from the treatment.

Another strength of this study is that the assessments will be carried out in two languages, while most other studies exclude non-Dutch speakers. All questionnaires used have been validated in both languages.

There are some limitations, however, that are worthwhile mentioning. First of all, we are unable for practical reasons to perform lengthy and costly diagnostic interviews, which means that we will not know how many participants in our study met the DSM criteria for depression. The results will, however, reflect the population whose symptoms are so distressing that they are willing to seek help. Secondly, the psychometric validities of the questionnaires used in this study have not yet been tested in an online environment.

## Abbreviations

AOC: Alles Onder Controle; AOC-TR: Alles Onder Controle TR (Adapted version); CES-D: Center for Epidemiologic Depression Scale; M.I.N.I.: Mini International Neuropsychiatric Interview; BDI-II: Beck Depression Inventory II; SOM: Somatization (subscale on the SCL-90-R); SCL-90-R: Symptom Checklist-90-Revised; LAS: Lowlands Acculturation Scale; EQ 5D: EuroQol Questionnaire 5D.
